## Abstract

**Context:**

Although teacher violence at schools is a serious problem in Haiti, there is a lack of systematic evidence on the effectiveness of school-based interventions in reducing teacher violence in this low-income country.

**Objective:**

To test the effectiveness of the preventative intervention *Interaction Competencies with Children for Teachers (ICC-T)* aiming to reduce teachers' use of violent disciplinary strategies and to improve their interaction competences with children in the Haitian context.

**Design, Setting, Participants:**

The study is designed as a two-arm matched cluster randomized controlled trial. The sample consists of 468 teachers and 1,008 children from 36 (community and public) primary schools around Cap-Haïtien (Département du Nord) in Haiti. Data will be collected in three phases, before the intervention, and 6 and 18 months after.

**Intervention:**

In the group of intervention schools, ICC-T will be delivered as a 5-day training workshop. Workshop sessions are divided into five modules: 1) improving teacher-student interactions, 2) maltreatment prevention, 3) effective discipline strategies, 4) identifying and supporting burdened students, and 5) implementation in everyday school life.

**Main Outcome Measure:**

The main outcome measure is teacher violence assessed in two ways: (i) teachers' self-reported use of violence, and (ii) children's self-reported experiences of violence by teachers.

**Conclusions:**

Prior evaluations of ICC-T had been conducted in sub-Saharan Africa with promising results. This study will test for the first time the effectiveness of this intervention outside the context of sub-Saharan Africa.

## Introduction

Corporal punishment is still a widespread phenomenon in schools worldwide, particularly in low-income countries (1). This practice consists of the use of physical force inflicted by teachers with the purpose of correcting a child's behavior and may include beatings with the use of hands or objects, such as a cane or stick, shaking, pinching or kicking students or forcing them to adopt painful bodily postures for a long time (2, 3). Research from around the world shows that corporal punishment can have negative and long-lasting repercussions on children's physical and emotional well-being (4, 5). In schools, corporal punishment has been related to decreased school performance and higher dropout rates (2). Despite having received less empirical attention, emotional violence by teachers, including practices such as belittling, ignoring and humiliating students, has also been related to increased levels of students‘ mental health problems and academic deficits (6–8). Through their effects at the individual level, disciplinary violence can hinder development at the country level (9). This is recognized in the United Nations' (UN) Development Agenda 2030, aiming to end all forms of violence against children as one of the UN's Sustainable Development Goals (SDG 16.2). Assessing the magnitude of teacher violence and devising effective prevention strategies is therefore an important step to promote development in low-income countries. The country of Haiti, ranking at 170 out of 189 countries in the Human Development Index, provides an appropriate setting to investigate the effects of reducing violence at school on children's well-being and psychosocial functioning.

Although Haiti has made significant progress in both getting children into school and addressing teacher absenteeism in recent years, school performance remains very poor^1^. Among the many obstacles that Haitian children face is violent discipline, despite increased efforts of the country to protect children in the past decades. In 1995, Haiti signed the Convention on the Rights of the Child, which protects children against all forms of violence (Art. 19). Corporal punishment of children at both home and schools is explicitly forbidden by the Law Against Corporal Punishment of Children (2001) (10). Accordingly, any person or authority who violates the physical integrity of a child will be dismissed and prosecuted under the Penal Code. If the offender is an institution—such as a school—its premises shall be closed. This law demands schools to establish a code of conduct to monitor and sanction offenders.

However, corporal punishment is still regularly practiced at both home and schools. The 2012 Violence Against Children (VAC) survey reveals that 67% of Haitian adolescents and young adults aged between 13 and 24 have experienced physical violence during childhood by a family member/caregiver or public authority figure (11). Of these, the most common perpetrators of disciplinary violence were mothers (47%) and fathers (40%), followed by aunts and uncles. Among public authority figures, the primary perpetrators are teachers (11). In an unpublished pilot feasibility study of the proposed intervention, Haitian primary school teachers named yelling at and insulting students, caning them, forcing them to kneel down or standing at the wall for a period of time as well as expelling them from the classroom as most common discipline methods at their schools.

Research suggests that those who extensively use corporal punishment as a disciplinary strategy do not tend to perceive it as a form of physical abuse, may be unaware of the negative consequences of this violence, and often lack the skills necessary to manage children's misbehavior in a non-violent way (12). In Haiti, nearly one-third of household heads believe that violence is necessary to educate children^2^. A study conducted in 39 primary schools in Haiti's Nord-Est department found that school principals view violence as a necessary tool to maintain discipline (13). Moreover, media accounts show that most parents in Haiti regard schools using disciplinary violence as rigorous and serious institutions^3^.

Another reason why corporal punishment at schools is so prevalent has to do with the lack of capacity of the Haitian state to train and monitor schools and teachers (14). Haiti has suffered a devastating earthquake in 2010, and more recently one in 2021. This is important since evidence shows that violence against children can intensify after disaster settings and situations of unrest or conflict (15–17). Eleven years after the earthquake, the need for schooling is still dire. Presently, there are no rules (at least not enforced) for opening a school or becoming a teacher in Haiti. In Haiti, 80% of primary schools are non-state schools (and three quarter of them operate without a license of the Ministry of Education)^4^. Furthermore, only 20% of primary school teachers receive formal basic pedagogical training^5^.

Although school violence has been banned in Haiti, teachers lack training in alternative disciplinary strategies. A survey of 30 teachers in four primary schools in the capital Port-au-Prince showed that most of them rejected the use of violence. They resort to it mainly because violence is allowed or encouraged at schools (18). Media reports also confirm that teachers resort to violence upon the instructions of school principals and/or the consent of parents^6^. Providing alternatives and changing beliefs around violent discipline in schools can thus be an important step toward development in this country.

A few interventions focusing on cultivating teachers' use of non-violent disciplinary strategies have shown to be effective in reducing the prevalence of corporal punishment at primary schools in low- and middle-income countries, including the Good School Kit in Uganda (9) and the Irie Classroom Toolbox in Jamaica (19). Currently, there is only one evaluated intervention focusing both on changing attitudes toward violence and on providing non-violent disciplinary methods, namely *Interaction Competencies with Children—for Teachers* (ICC-T) (3, 20, 21). Although violent discipline at schools is a serious problem in Haiti, we lack systematic evidence on the effectiveness of school-based interventions in reducing teacher violence in this low-income country.

The purpose of this study is to evaluate the effectiveness of ICC-T in reducing teacher violence in Haitian primary schools through a two-arm matched cluster-randomized controlled trial (CRCT). In this study, violence by teachers refers to acts of both physical and emotional violence. Prior CRCTs of this intervention had already been undertaken in Tanzania and Uganda (3, 20, 21). Results suggest that ICC-T is a successful strategy to reduce violence by teachers and improve teacher-child relationships. While promising, the effectiveness of ICC-T in other low-income countries outside sub-Saharan Africa has not been tested yet. The proposed study will thus be the first CRCT testing ICC-T in the Western Hemisphere.

## Methods and Analysis

### Study Design and Sampling

The study is designed as a two-arm matched cluster-randomized controlled trial. It will be based on (at least) 36 primary schools from six of the overall 19 communes in the *Départment du Nord* in Haiti. For logistical reasons, this study will focus on the six communes in which all schools are reachable within 2 h drive from *Cap-Haïtien*, the capital of the *Départment du Nord: Cap-Haïtien, Quartier-Morin, Limonade, Acul-du-Nord, Plaine-du-Nord* and *Milot*. As there are only few schools in the commune *Quartier-Morin*, the schools in this commune will be combined with those schools in the two neighboring communes *Dondon* and *Grande-Rivière-du-Nord* that are reachable from *Cap-Haïtien* within 2 h. Three data collection phases will be undertaken: a baseline (pre-) assessment before the intervention (t_0_), a first follow-up assessment ~6 months after the intervention (t_1_) and a second follow-up 18 months after the intervention (t_2_). The study flowchart is displayed in Figure 1, while the timeline is shown in Figure 2. The estimated total costs of the project amount to US $ 220,000.

**Figure 1 F1:**
[figure not shown]
Flow chart of the study design.

**Figure 2 F2:**
[figure not shown]
Study timeline.

### Power Calculation

We conducted an *a priori* power analyses to determine the number of clusters (schools) for the trial as well as the number of participants (students and teachers) per cluster. Following a previous trial of ICC-T at Tanzanian secondary schools (21), we expected moderate (δ = 0.25) and large effects (δ = 0.35) on student-reported and teacher-reported violence by teachers, respectively. Based on previous and ongoing trials of ICC-T (3, 20, 21), we expected an intra-class correlation coefficient (ICC) of 0.03 and 0.05 for student- and teacher-reported violence, respectively. Moreover, the covariance between baseline and follow-up scores of violence at the school level was *r* = 0.30. Given all specified parameters (α = 0.05; power = 0.80; effect size students: δ = 0.25, effect size teachers: δ = 0.35; ICC students = 0.03, ICC teacher = 0.03; *R* = 0.30), no drop out at the school-level and an estimated dropout rate of 30% for teachers and 25% for students, in total 36 schools with 28 students and 13 teachers per school are required to detect the expected effects. The total sample size is therefore at least *n* = 1,008 children and *n* = 468 teachers.

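### The power calculation gives two teacher ICCs (0.05 expected, 0.03 entered) and leaves the 0.30 baseline association undefined; stated power of 80% may be up to about 5 points too high

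*Protocol article*

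**What the plan says.** Everything at issue stands in one paragraph of the protocol article, under Power Calculation.

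- **Expected ICCs**, attributed to previous and ongoing trials of the intervention: "we expected an intra-class correlation coefficient (ICC) of 0.03 and 0.05 for student- and teacher-reported violence, respectively".
- **ICCs listed as inputs**: "ICC students = 0.03, ICC teacher = 0.03".
- **Baseline adjustment**: "the covariance between baseline and follow-up scores of violence at the school level was" r = 0.30. The input list then writes it as R = 0.30.
- **Error rate and target**: "α = 0.05; power = 0.80". Sidedness is not given.
- **Effects**: "effect size teachers: δ = 0.35" and "effect size students: δ = 0.25".
- **Attrition**: "an estimated dropout rate of 30% for teachers and 25% for students", with none at school level.
- **Result**: "in total 36 schools with 28 students and 13 teachers per school are required to detect the expected effects".

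Under Study Measures, teacher self-report is one of the two measures of the main outcome. Under Schools, having at least 13 teachers is an inclusion criterion that refers back to the power calculation. Under Participants, all teachers in a selected school are to be included, so 13 is a minimum.

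**The concern.** The two teacher ICCs cannot both be the planning value. 0.05 is the only one with a stated empirical basis, and 0.03 is the one listed among the inputs that lead to 36 schools and 13 teachers. A higher ICC means more between-school variance and lower power at a fixed number of schools. If the planning value is 0.05 and 0.03 was entered, the 80% stated for the teacher outcome is too high.

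The 0.30 raises a separate doubt. Read as a correlation, it removes 0.30² = 9% of the school-level variance. Read as R², it removes 30%. The paragraph supports neither reading over the other, and stated power for both outcomes depends on the choice.

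At stake is whether the power printed for the two main outcome measures follows from the printed inputs.

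**Working it through.** **Inputs.** From Power Calculation: 36 schools; 13 teachers and 28 students per school; dropout 30% and 25%; effects 0.35 and 0.25 SD; the ICCs above; 0.30. From Schools: three schools per arm in each of six communes, so 18 against 18. My assumptions: two-sided test, baseline adjustment at school level only, t reference with 36 − 2 = 34 df.

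Retained per school: teachers 13 × 0.70 = 9.1; students 28 × 0.75 = 21.

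**Formula.** Var(difference) = (4/36) × [ICC × (1 − R²) + (1 − ICC)/m]. Power comes from the noncentral t with noncentrality δ/√Var.

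**Step 1: reproduce the stated design (teacher ICC 0.03).**

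- R² = 0.30: Var = (4/36) × (0.0210 + 0.97/9.1) = 0.01418; SE 0.1191; 0.35/0.1191 = 2.94; power **81.5%**.
- R² = 0.09: Var = (4/36) × (0.0273 + 0.97/9.1) = 0.01488; SE 0.1220; ratio 2.87; power **79.6%**.

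The stated 80% is reproduced.

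**Step 2: change only the teacher ICC to 0.05.**

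- R² = 0.30: Var = (4/36) × (0.0350 + 0.95/9.1) = 0.01549; SE 0.1245; ratio 2.81; power **78.0%**; effect detectable with 80% power 0.359.
- R² = 0.09: Var = (4/36) × (0.0455 + 0.95/9.1) = 0.01666; SE 0.1291; ratio 2.71; power **75.0%**; detectable effect 0.372.

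**Step 3: students (ICC 0.03, not in dispute).**

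- R² = 0.30: Var = (4/36) × (0.0210 + 0.97/21) = 0.00747; SE 0.0864; ratio 2.89; power **80.3%**; detectable effect 0.249.
- R² = 0.09: Var = (4/36) × (0.0273 + 0.97/21) = 0.00817; SE 0.0904; ratio 2.77; power **76.7%**; detectable effect 0.261.

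**Step 4: which convention fits both designs?** With t on 34 df and school-level R² = 0.30, 80% power at 36 schools needs:

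- 20.9 retained students, rounded to 21, and 21/0.75 = 28;
- at ICC 0.03, 8.7 retained teachers, rounded to 9, and 9/0.70 = 12.9, rounded to 13.

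Both printed cluster sizes come out. With teacher ICC 0.05 the same convention needs 9.8 retained teachers, and 9.8/0.70 = 14.0.

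**Step 5: sensitivity to the convention.** Normal approximation in place of t:

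| Adjustment | Teachers, ICC 0.03 | Teachers, ICC 0.05 | Students, ICC 0.03 |
|---|---|---|---|
| None | 81.1% | 76.2% | 77.6% |
| R² = 0.09, school level | 81.9% | 77.4% | 79.0% |
| R² = 0.30, school level | 83.6% | 80.3% | 82.5% |
| r = 0.30 (R² = 0.09), both levels | 84.6% | 80.0% | 81.3% |

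Two of these conventions reach 80% for teachers at ICC 0.05.

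**Step 6: size of the gap in design terms (t reference, ICC 0.05).** At 36 schools, 80% would take 14 teachers per school if R² = 0.30, or 16 if r = 0.30. At 13 teachers per school it would take 38 or 42 schools.

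**The case against.** The strongest reply is that the listed 0.03 may be a misprint. The article names no software, formula, sidedness or reference distribution. If 0.05 was entered and one digit was typed wrongly, no power was lost. The last row of the table makes this more than a formality: a normal approximation with r = 0.30 applied at both levels meets 80% for both outcomes at the expected ICCs, with 0.30 read as an ordinary correlation. Against this, the text places the 0.30 at school level, and the convention that returns both printed cluster sizes uses ICC 0.03. A misprint is therefore not the best-fitting explanation, but it cannot be excluded. For the same reason it cannot be said that 36 schools for students requires R² = 0.30.

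A second reply is that the trial may retain more than 9.1 teachers per school, because all teachers are included and 13 is a minimum. That stands. With 11 retained teachers at ICC 0.05, power on the t reference is 80.2% (R² = 0.09) or 83.3% (R² = 0.30). The Statistical Analysis section also plans multilevel models over three waves with full information maximum likelihood, which the simple two-group comparison above does not represent.

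A reader might therefore be tempted to conclude that the calculation was run with the wrong ICC and that the trial will deliver only 75–78% power. The documents do not support that: they do not show which value was used, which ICC is right, or how many teachers will be retained.

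**Conclusion.** The contradiction in the teacher ICC is certain, because both values are printed and nothing reconciles them. The ambiguity of the 0.30 is equally plain. Their numerical effect is small and depends on the convention.

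- **Teachers at ICC 0.05:** 0 to 5 points below the stated 80%, and about 2 points under the convention that best fits both printed designs.
- **Students on the t reference:** no shortfall if 0.30 is R², and about 3 points if it is a correlation.

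These figures assume a two-sided test, 18 schools per arm, and exactly the planned minimum numbers less the stated dropout. The stated power needs correcting or justifying because it concerns a main outcome measure. The point does not show that the trial is underpowered in any important sense, and it gives no reason to change the number of schools.

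**What to change.** In the Power Calculation paragraph:

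1. Reconcile the two teacher ICCs and use one value throughout. 0.05 is the natural default for the rerun, as the only one given an empirical basis. If 0.03 is intended, give the reason.
2. State whether 0.30 is a correlation or a share of variance explained, and at which level it applies. Replace the word covariance and use one symbol.
3. State sidedness and the reference distribution or software, then rerun for both outcomes.
4. Restate power, or the detectable effect at 80% power, with 36 schools held fixed. On the t reference with teacher ICC 0.05, that is about 78% or an effect of 0.36 for teachers if 0.30 is R², with students at about 80% and 0.25. If 0.30 is a correlation, it is about 75% or 0.37 for teachers and about 77% or 0.26 for students.
5. Note that 13 teachers per school is a minimum, so realised power may be higher.

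The cost is one corrected paragraph and possibly a slightly lower stated power. No schools are added, and no outcome or analysis changes.

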### Schools

Selected schools must meet the following inclusion criteria: (1) teachers should not have received any training on violence prevention in the past; (2) the school should be a community or public mixed-gender school; (3) the school should have at least 13 teachers and at least 40 children in the 4th class of primary school (see power calculation above). In case of fewer than 13 teachers or fewer than 40 students in the relevant grade, the selected school will be combined with a neighboring school (within 15 km) into a school cluster. Schools that meet these criteria will be listed in alphabetical order and a random selection of six schools/school clusters in each of the six communes of Haiti's Département du Nord will be executed using http://www.random.org. In each commune, three schools or school clusters will be allocated to the treatment group (i.e., teachers will receive the ICC-T sessions), and the other three schools or school clusters into the control group (i.e., teachers will not receive the ICC-T sessions) after baseline assessment. All random selections and allocations will be performed by independent research staff.

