### Statistical Analysis

Pre-assessment data will be used to assess the prevalence of maltreatment and violence as well as children's mental health and well-being. A longitudinal analysis (including the follow-up assessments) will then be undertaken using an intent-to-treat approach. As drop-outs and missing data at follow-up assessment are likely given the longitudinal study design, we aim to apply full information maximum likelihood estimation to obtain unbiased parameter estimates.

Our main analysis of the primary and secondary outcomes will be time × group interaction effects using multilevel linear modeling. By randomly assigning schools to the intervention and control condition, we do not expect systematic differences between schools, teachers, and students in the two groups. However, we will examine differences between the groups in sociodemographic characteristics on the level of the school (e.g., material conditions), teachers (e.g., socioeconomic status, teaching experience) and students (e.g., socioeconomic status, gender). In case of significant differences, we will control for these differences in all analyses. Latent growth modeling or cross-lagged path models will be used to estimate the directional influence of violence by teachers on primary and secondary outcome variables over time. Results will be presented including appropriate effects sizes and with a measure of precision (95% confidence intervals). Effect sizes of η^2^ ≥ 0.01, η^2^ ≥ 0.06 and η^2^ ≥ 0.14 will be considered as small, moderate, and large effects, respectively (47).

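### Schools are randomised 3:3 within six communes, but the stated main analysis does not name commune; including it with its time interaction is a cheap safeguard for precision

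*Protocol article*

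**What the plan says.** The Schools section of the protocol article describes "a random selection of six schools/school clusters in each of the six communes of Haiti's Département du Nord", then allocation after baseline: "In each commune, three schools or school clusters will be allocated to the treatment group", with the other three going to control. That gives 18 schools per arm in six blocks of six. Study Design and Sampling adds that the Quartier-Morin stratum is merged with reachable schools in two neighbouring communes.

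The same section labels the trial: "The study is designed as a two-arm matched cluster-randomized controlled trial". No pair, matching variable or matching step is described in the article.

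The Statistical Analysis section gives the model: "Our main analysis of the primary and secondary outcomes will be time × group interaction effects using multilevel linear modeling". It does not name commune. Groups are to be compared on sociodemographic characteristics of schools, teachers and students, followed by this rule: "In case of significant differences, we will control for these differences in all analyses".

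**The concern.** Blocking by commune removes differences between communes from the comparison of arms. A model without commune still counts those differences as error, so its standard error can exceed the true variability of the estimate. The result is a test below its nominal level, wide intervals and some lost power.

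The covariate rule makes this more than plain silence. Commune is split 3:3 in every block, so a test for baseline imbalance would not be expected to flag it. The only published route for adding covariates therefore does not lead to the stratifier.

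The power target leaves little slack, as the reproduction below shows, so avoidable loss of precision matters somewhat. The label 'matched' is a lesser issue: it is undefined, and it sits beside a procedure that is stratified allocation.

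**Working it through.** **1. The plan's own figure.** Inputs from Power Calculation: "α = 0.05; power = 0.80; effect size students: δ = 0.25, effect size teachers: δ = 0.35; ICC students = 0.03, ICC teacher = 0.03", R = 0.30, 36 schools, and "no drop out at the school-level and an estimated dropout rate of 30% for teachers and 25% for students". After dropout there are 28 × 0.75 = 21 students and 13 × 0.70 = 9.1 teachers per school. I read R as the share of school-level variance explained by baseline and α as two-sided:

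SE = √[(4/36) × (ICC × (1 − 0.30) + (1 − ICC)/m)], non-central t on 33 df.

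- Students: √[(4/36)(0.021 + 0.0462)] = 0.0864, power 0.802.
- Teachers, ICC 0.03: √[(4/36)(0.021 + 0.1066)] = 0.1191, power 0.814.

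The 36 schools reproduce, with no gain from stratification claimed. The text also says "we expected an intra-class correlation coefficient (ICC) of 0.03 and 0.05 for student- and teacher-reported violence, respectively". At the teacher value of 0.05, power at 36 schools is 0.779 and 38 are needed. That discrepancy does not depend on commune.

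**2. Effect of omitting commune on the change contrast.** The planned effect is time × group, so I work with each school's change from baseline to one follow-up. Let f be the share of between-school variance that lies between communes, r the correlation of commune and school effects over time, and ρ the correlation over time of the within-school error of the school means.

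- Commune part: v_c = 2(1 − r) × f × ICC
- Remainder: v_s = 2(1 − r)(1 − f) × ICC + 2(1 − ρ)(1 − ICC)/m

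With 3:3 blocks, v_c drops out of the true variance of the arm difference. Without commune in the model, each arm's sample variance picks up 3 × 5 × v_c / 17 = (15/17) v_c. The interval width without commune, relative to with it, is about

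(t₃₄/t₂₉) × √(1 + (15/17) v_c/v_s), with t₃₄/t₂₉ = 2.032/2.045 = 0.994.

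Assumptions: f = 0.25 or 0.50 (not in the article), r = 0.30 (the school-level figure in Power Calculation, applied to communes too) and ρ = 0.5 (not in the article). Then 2(1 − r) = 1.4 and 2(1 − ρ) = 1.

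| Outcome | f | v_c | v_s | Width ratio |
|---|---|---|---|---|
| Students, ICC 0.03 | 0.25 | 0.0105 | 0.0315 + 0.0462 = 0.0777 | 1.05 |
| Students, ICC 0.03 | 0.50 | 0.0210 | 0.0210 + 0.0462 = 0.0672 | 1.12 |
| Teachers, ICC 0.05 | 0.25 | 0.0175 | 0.0525 + 0.1044 = 0.1569 | 1.04 |
| Teachers, ICC 0.05 | 0.50 | 0.0350 | 0.0350 + 0.1044 = 0.1394 | 1.10 |
| Teachers, ICC 0.03 | 0.25 | 0.0105 | 0.0315 + 0.1066 = 0.1381 | 1.03 |
| Teachers, ICC 0.03 | 0.50 | 0.0210 | 0.0210 + 0.1066 = 0.1276 | 1.06 |

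Simulation of school means (20,000 runs per cell) agrees. At f = 0.50, without against with commune:

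- Students: type I error 0.029 against 0.049, power 0.73 against 0.80.
- Teachers (ICC 0.05): type I error 0.033 against 0.052, power about 0.71 against 0.77.

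At f = 0.25 type I error without commune is about 0.04. A baseline-adjusted follow-up model gives similar width ratios.

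**3. Sensitivity to the reading of R.** If 0.30 is a variance share, as in step 1, the correlation is √0.30 = 0.548 and 2(1 − r) = 0.905. The same formula then gives 4% and 9% for students, and 3% and 7% for teachers at ICC 0.05 (f = 0.25 and 0.50).

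**4. When nothing is lost.** If commune effects are fully stable, v_c = 0. Simulated change scores for teachers (ICC 0.05, 9 per school) gave type I error 0.051 with and without commune at f = 0.25. Mean interval width was 0.690 without and 0.694 with. At f = 0 the interval is likewise about 0.5% narrower without commune.

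**5. Which commune term matters.** Adding only commune main effects to a group × time model with a school random intercept left the interaction estimate unchanged in three simulated balanced datasets. Its SE barely moved (0.1490 and 0.1490; 0.1566 and 0.1567; 0.1539 and 0.1539). Only commune × time terms remove commune-specific change from this contrast.

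**The case against.** The strongest counter-argument is that the planned contrast uses baseline, so a stable commune difference subtracts out and omission costs nothing. This stands for fully stable effects (step 4). It does not dispose of the point. The article puts the school-level association between baseline and follow-up at only 0.30, and if communes behave similarly, most of their variance does not cancel. How stable commune effects really are is unknown.

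Second, the article is silent on commune and does not exclude it. It gives no random-effects structure, and stratification terms are commonly set out in a full protocol or SAP, which is not at hand. This stands as a limit: a reader might infer that commune has been ruled out, and the text does not say so. What can be raised is that the published covariate rule would not be expected to admit it.

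Third, any error is conservative, so there is no added risk of a false positive. That also stands.

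On the label, a reader might infer that the trial is matched on nothing, or that a paired analysis is intended. Schools are grouped by commune before allocation, so 'matched' may be loose wording for blocking, and no paired analysis is mentioned.

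**Conclusion.** The point holds as a cheap improvement. The trial randomises within commune, and its stated main model does not name commune. At the ICCs the article expects (0.03 students, 0.05 teachers), omission would widen intervals by roughly 4% to 12% and lower type I error to about 0.03 to 0.04. This rests on an assumed commune share of 25% to 50%, a correlation of 0.30 over time for both commune and school effects, and an assumed within-school error correlation of 0.5. The loss is smaller at a teacher ICC of 0.03 or with more stable effects, and nil if commune differences are absent or fully stable.

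A reader might conclude that the gain from stratification is certainly lost and the intervals certainly too wide. The article gives no commune variance, so that certainty is not supported. Treatment estimates are not biased, allocation still balances communes, and the 36 schools are unaffected. The wording of 'matched' is a minor matter.

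**What to change.** - In every time × group outcome model, include the six allocation strata (Quartier-Morin merged with its neighbours, as allocated) as fixed effects together with their interaction with time. In a baseline-adjusted follow-up model, stratum fixed effects alone suffice.
- Do this regardless of any baseline significance test, and say that the covariate rule does not govern the stratification factor.
- Describe the design as a commune-stratified cluster randomised trial, or state what 'matched' means.

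The cost is wording plus 5 of the 34 between-school degrees of freedom for a follow-up contrast, which widens intervals by about 0.5% if commune explains nothing. Sample size and data collection do not change.
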